### Design

The study will be a pretest posttest independent measures design with a five level experiment consisting of a control group and a 2 × 2 design for type of feedback (intrinsic or KR) and presence of topic contingent KP feedback in the form of articulation guidance. See Figure 3 for an overview of the aims, variables, outcomes and measures employed in this experiment.

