### Outcome measurement

The relative benefits of the different experimental conditions will be measured by the primary measure of changes in use of phonological processes and PCC from pre-test to post-test as measured by the DEAP (Dodd et al., 2002). Such assessment will capture suppression of the phonological processes targeted in treatment and generalization effects (if any) to other phonological processes. Phonological process percentage of occurance (Randolph and Wendt, 2014; i.e., the number of times that a child uses a given phonological process) will also be measured and compared pre and posttest. Pre and post-test assessments will be recorded and a sample of the assessments independently analyzed followed by interrater reliability checks. In addition to the pre-test/post-test measures, number of trials and percentage accuracy of trials per session (cumulative accuracy) will be measured for each experimental condition as further indication of the effectiveness of feedback of that condition and determine when goals of intervention have been reached. For example, if a child reaches 90% accuracy of production of target words for one phonological process, another will be targeted. It could be argued that motivation to continue playing will increase practice and consequently improve outcomes (Williams, 2012). A secondary measure of motivation as a variable that could influence the effectiveness of feedback type will be the amount of time participants choose to continue playing the game (Deci et al., 1999) up to a total of 20 min as well as the number of trials they complete.

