## Proposed analysis

The assessments of speech production will be transcribed to an Excel spreadsheet. Statistical analysis will be performed using the Statistical Package for the Social Sciences (IBM SPSS Statistics 24).

The key question to be addressed in this research is: How does feedback type during speech therapy session influence children's production performance. As such, the key dependent variable under analysis will be PCC, phonological process percentage of occurrence and percentage accuracy of trials. Published data of PCC in children's development (e.g., Dodd et al., 2002) suggest that this variable to be normally distributed. As such we intend to perform a full-factorial regression analysis on PCC with feedback condition, number of trials completed, and child age (4, 5, or 6 years) and severity as predictor variables. The full-factorial nature of this analysis will allow us to determine how the effects of condition and trials completed independently predict PCC and the extent to which these factors interact in their effects on PCC between pretest and post-test. For example, we may find that with certain types of feedback, the number of trials completed has a much greater effect than with other types of feedback. Similarly, we may find that some feedback types have a greater effect on performance for younger or older children. These analyses will also be completed with phonological process percentage of occurance at pretest and post-test and percentage accuracy of trials as a dependant variables

We will also conduct a Generalized Linear Model Analysis assuming a binomial distribution for the number of correct trials post “intervention” within a total of *n* trials where *n* may differ between children. The analysis will control for pre “intervention” language skills, age, and gender. Marginal means will be compared for the five groups using a Bonferroni correction for multiple comparisons. This analysis could assist in distinguishing the effects of real-world simulation vs. verification feedback and the presence of articulation guidance.

Motivation to persevere could be considered a variable that mediates the impact of type of feedback. Consequently, we will also perform a one-way ANOVA to determine how feedback condition influences motivation as measured by the number of trials and the duration of game play.

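### The regression names pre-test and post-test scores as outcomes but lists no change score, pre-test covariate, time term or child term, so its condition effect is not tied to the primary measure of pre-to-post change

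*Protocol article*

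**What the plan says.** - **Protocol article, Design:** the trial is a "pretest posttest independent measures design", so each child gives two DEAP scores and belongs to one of five groups.
- **Outcome measurement:** the conditions are compared on the "primary measure of changes in use of phonological processes and PCC from pre-test to post-test".
- **Proposed analysis:** the main model is given as "full-factorial regression analysis on PCC with feedback condition, number of trials completed, and child age (4, 5, or 6 years) and severity as predictor variables". It is added that this model will show how condition and trials act, and interact, on PCC from one test to the other. It then says "These analyses will also be completed with phonological process percentage of occurance at pretest and post-test", with trial accuracy as a further dependent variable.
- **Proposed analysis, second model:** a separate binomial model for correct trials does name a pre-intervention adjustment (language skills). The PCC regression names none.
- **Session schedule:** the pre-test is taken after allocation but before any game session.

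**The concern.** The primary measure is a change, so the analysis needs something that represents change or conditions on the starting score: a difference, a pre-test covariate, or a condition-by-time term with a child effect. The listed predictors contain none of these. Calling the model full-factorial does not supply one, because it only crosses the factors listed and time is not among them.

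For process occurrence, the pre-test value is itself named as an outcome. Feedback not yet given cannot affect it.

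At stake is which estimate is reported for the primary outcomes. The wording leaves open post-test, change, or both scores together, and these do not all estimate the same quantity. A choice left open here could be made after the data are seen.

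**Working it through.** **Inputs from the protocol.** Five groups of 30 (150 children); f = 0.32, 5% significance, 80% power; predictors as quoted; severity graded from DEAP PCC (Participants). The pre-post correlation ρ is not given, so 0.3 to 0.8 is assumed.

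**The plan's own figure.** For a one-way ANOVA with five groups, the noncentral F with λ = N·f² needs N = 122 (125 for equal groups) for 80% power. At N = 150, λ = 150 × 0.32² = 15.36 and power is 0.888. The stated 150 is therefore not reproduced as a one-way ANOVA, and the protocol names no test. This does not bear on the present point, but 0.888 is a useful benchmark below.

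**What the condition term estimates.** Let Δ be the true between-arm difference in post-test means. Randomisation makes expected pre-test means equal, so Δ is also the expected difference in change.

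1. *Both scores in one model, no time or child term:* contrast = ½(pre-test difference + post-test difference), with expectation ½(0 + Δ) = Δ/2 at any correlation.
2. *Pre-test alone:* expectation 0. It shows only chance imbalance.
3. *Post-test alone:* expectation Δ.
4. *Change score:* expectation Δ − 0 = Δ.
5. *Post-test with pre-test as covariate:* expectation Δ. Using change as outcome with the pre-test covariate gives the identical condition estimate.

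**Size.** Arm means were equally spaced in proportion to −2, −1, 0, 1, 2. Their root mean square is √(10/5) = 1.414, so each step is 0.32/1.414 = 0.2263 SD and the extreme arms differ by 4 × 0.2263 = 0.905 SD. Half of that is 0.453.

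Simulation, 3,000 runs per setting: pre-test N(0,1); post-test = ρ × pre-test + noise + 0.5 + arm mean; severity as thirds of the pre-test score. Age and trials were left out. All rows include severity, as the protocol's model does.

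| Outcome used | Extreme-arm estimate (true 0.905) | Power, ρ = 0.3 / 0.5 / 0.7 / 0.8 | Type I error over the range |
|---|---|---|---|
| Both scores in one model | 0.45 | 70 / 78 / 87 / 93% | 3–10% |
| Change score | 0.90–0.91 | 88 / 94 / 100 / 100% | 5–6% |
| Post-test alone | 0.90–0.91 | 91 / 95 / 99 / 100% | 4–6% |
| Post-test with pre-test covariate | 0.90–0.91 | 92 / 96 / 100 / 100% | 4–6% |
| Pre-test alone | 0.00 | 4–5% (nothing to detect) | 4–5% |

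Without severity, post-test alone gives 88 to 89% power, in line with the 0.888 above. The one-model version without severity has type I error of 10 to 23%, but severity is in the protocol's list, so that figure does not describe the plan.

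**The case against.** A reader might infer that the plan pools the paired scores as independent rows and so halves its treatment effect. The document does not support this. Nowhere does it say that pre-test and post-test rows are pooled. The sentence on interactions speaks of PCC from one test to the other, and Outcome measurement speaks of change. Read together, these suggest that change was meant.

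A reader might also infer that separate pre-test and post-test regressions would miss the primary measure altogether. That is wrong for the post-test model: in a randomised comparison its condition contrast has the same expectation as the contrast in change. Severity is itself derived from DEAP PCC, so part of the baseline adjustment is already present. The pre-test regression is then redundant but harmless.

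It can also be argued that coding a two-time-point outcome is commonly left to an analysis plan that is not shown. That would answer silence. Here the article gives its predictor list, names pre-test values of process occurrence as an outcome, and states a baseline adjustment for the other model. What stands against it is a stated specification that does not match the stated primary measure.

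**Conclusion.** The mismatch is real, but its harm is conditional. As listed, the regression does not tie its condition effect to the primary pre-to-post change, and pre-test scores have no place as an outcome.

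- If both scores entered one such model, the estimate would be half the true effect whatever the correlation. Pairing would be ignored, and power would be about 70 to 93% against 88 to 100% for change scores.
- If change scores or post-test scores alone are used, there is no bias and little loss.

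The halving is arithmetic. It needs only that the pre-test is unaffected by allocation; the pre-test follows allocation, but its assessor is blind to condition. The power and type I error figures rest on the assumed correlations, equally spaced arm means, and a simplified model without age and trials.

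**What to change.** In Proposed analysis, for PCC and for process occurrence:

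- Use one dependent value per child: the post-test score with the pre-test score as covariate, or the change score adjusted for the pre-test score.
- Alternatively, fit a mixed model to both scores with a random child effect, time and condition-by-time, and take condition-by-time as the treatment effect. If age and severity stay in that model, let them interact with time as well.
- Remove pre-test scores as an outcome.
- Report the condition effect from a version without number of trials. Trials are counted after randomisation and the control group does not play the game, so with trials and its interactions in the model the condition term is not the randomised between-arm contrast. The full-factorial model can remain as exploratory.

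The cost is wording only. Both scores are already to be collected, and SPSS fits either model.

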### Session schedule

Dosage is a significant variable in intervention for speech sound disorders (Baker, 2012; Kaipa and Peterson, 2016) and relates to the number of treatment sessions, the frequency of treatment sessions, length of treatment sessions and number of trials per treatment session (Baker, 2012). A clear precedent has not been set in the literature as to the most effective or efficacious dosage for phonological therapy, let alone home practice (which the study is aiming to investigate). There is evidence to suggest that treatment should occur three times per week (Allen, 2013) but daily home practice is also used (Crosbie et al., 2005). The number of sessions rarely exceeds 16–21 sessions in total in studies of phonological therapy (Crosbie et al., 2005; Williams, 2012). Despite the novelty of the study in exploring practice with an app the above literature will be used as a guide such that each participant will attend the Swinburne Babylab facility for individual sessions 3–4 days per week over a 2–4 week period for a total of 12 sessions (in addition to testing sessions). As the study seeks to investigate the number of trials (from data on percentage accuracy per trial) and length of session as measures of effectiveness of feedback and motivation, respectively, these parameters of dosage will not be set but we expect that children will engage for up to 20 min completing 80–100 trials.

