At the start of the first session children will be evaluated by a qualified speech pathologist with experience in the assessment of children with speech sound disorders to confirm that they fit within the inclusion criteria. This step will be accomplished by collecting a case history and include questions relating to the inclusionary and exclusionary questions as well as previous exposure to speech pathology intervention and speech pathology apps. During this assessment session, the speech pathologist will work through a checklist of instructions which are exemplary of instructions used in the therapy task to ascertain the stimulability of the therapy targets and that the child's comprehension of the instructions to be used in the experimental tasks. Errors in comprehension will be corrected by the speech pathologist within this session. Participants will be randomly assigned to a feedback condition or to the control condition and then take the pre-test. The pre-test and post-test will be offered in a room separate from the Babylab to reduce encoding specificity effects that would provide an advantage to the children in the feedback condition relative to those in the control condition. The control group will attend the first session and then return between 2 and 4 weeks later to take posttest. After completing the pretest, the experimental group will be offered 12 sessions of the experimental activities over a 4-week period. The experimental groups will then be familiarized with the Babylab. Each of sessions two to 12 will consist of approximately 10 min for the experimental task followed by approximately 10 min of an unrelated game or activity for an expected total of 20 min. Children will determine when they want to stop playing the experimental activity. As stated above, the children will complete 80–100 trials of the target minimal pairs but the exact number of trials completed by each child for each session will be recorded and checked for equity between participants. On completion of the experimental task in session thirteen, children will move from the Babylab to take the post-test. See Figure 4 for a diagram of the session schedule.

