## Anticipated results

With respect to research question 1, this study aims to investigate the effectiveness of four different types of feedback in improving speech sounds in young children while using a multimedia platform. Each of the three theoretical frameworks for learning discussed in the Background section predict that KR, the prevalent feedback in speech learning applications, will be the least effective because it does not contain information to assist learners in improving their speech production (Shute, 2008). The conversational framework for multimedia learning predicts that intrinsic feedback will be more effective than KR feedback because it is most likely to resemble real-world speech learning experiences which can be built upon (Laurillard, 2002). This framework predicts that the most effective feedback overall will be intrinsic combined with topic contingent KP because children will be able to elaborate and refine knowledge gleaned from real-world experiences with lessons learned during speech pathologist/learner dialogue (Laurillard, 2002). Within the context of novice-expert learning (Mason and Bruning, 2001; Moreno, 2004) children who are more responsive to therapy (influenced by factors such as age and severity of disorder) might benefit from KR combined with topic contingent KP, possibly because they could benefit from smaller amounts of more focused feedback. This combination is also prevalent in speech pathology practice.

With respect to research question 2, the prediction that the two conditions with intrinsic feedback will be the most effective in improving speech production is accompanied by the prediction that these two conditions will also be the most motivating because they will be situated in natural and social scenarios that could be more visually appealing, possibly more challenging (Mayer, 2014b) while offering greater autonomy and relevance (Ryan et al., 2006) and consequently should encourage more trials and longer gameplay. We also anticipate that other features of the respective feedback types will emerge from the analysis to suggest variables that will improve their effectiveness.

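### The binomial model on correct trials treats a child's trials as independent and weights each child by number of trials, although the child is the randomised unit

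*Protocol article*

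**What the plan says.** Under Proposed analysis the article plans regressions on three child-level outcomes, one of them percentage accuracy of trials. It then adds: "We will also conduct a Generalized Linear Model Analysis assuming a binomial distribution for the number of correct trials post". The count is thus taken after the intervention, and its denominator is given as "trials where *n* may differ between children". This second model adjusts for pre-intervention language skills, age and gender. Marginal means of the five groups are compared with a Bonferroni correction, and the stated purpose is to help separate real-world simulation from verification feedback and to show the effect of articulation guidance. The description includes no child effect, no overdispersion term and no per-child weighting.

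If n counts game trials, it is not fixed by design. Session schedule says of the number of trials and session length that "these parameters of dosage will not be set but we expect that children will engage for up to 20 min completing 80–100 trials", and also: "Children will determine when they want to stop playing the experimental activity". The number of trials is itself an outcome, because a one-way ANOVA is to "determine how feedback condition influences motivation as measured by the number of trials and the duration of game play". Anticipated results predicts that the intrinsic conditions "consequently should encourage more trials and longer gameplay". Outcome measurement says it could be argued that "motivation to continue playing will increase practice and consequently improve outcomes".

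**The concern.** Children are randomised, so evidence about a feedback type accumulates by child. Ninety responses from one child share that child's ability and are not ninety independent observations. A plain binomial model ignores this, takes its standard error from the total number of trials, and can declare differences that are only chance imbalance between children.

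A separate issue concerns the estimate itself. In a binomial model a child with three times the trials has three times the weight. If keen children are also more accurate, and more so under one feedback type than another, group means can differ although the average child is equally accurate in each. Correcting the standard error does not remove this shift.

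At stake are the corrected group comparisons meant to tell the feedback types apart.

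**Working it through.** **Inputs from the article.** 30 children in each of five conditions; 80 to 100 trials expected, midpoint 90; n free to vary by child; Bonferroni correction. If all pairs are compared there are 5 × 4 / 2 = 10, so the level per pair is 0.05 / 10 = 0.005 and the critical value is 2.807. The article gives no figure of its own for this point that could be reproduced.

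**Assumed, because the article does not give them.** Mean accuracy 0.65; between-child SD of accuracy (after covariates) 0.15 to 0.18 for step 1 and 0.15 to 0.20 for step 2; correlation r of n with accuracy 0.3 to 0.5; coefficient of variation (CV) of n as stated below.

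**Step 1: standard error.** The intra-child correlation is SD² / [p(1 − p)], and with equal n the variance is understated by the factor 1 + (n − 1) × correlation.

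- SD 0.15: 0.0225 / 0.2275 = 0.0989; 1 + 89 × 0.0989 = 9.80; square root 3.13. The effective critical value is 2.807 / 3.13 = 0.897, so the false-positive rate per pair is about 37%.
- SD 0.18: 0.0324 / 0.2275 = 0.1424; 1 + 89 × 0.1424 = 13.7; square root 3.70. The effective critical value is 0.759, so the rate is about 45%.

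Simulation of null scenarios, some with unequal n, gave about 36 to 49% per pair. A five-arm simulation with Bonferroni over ten pairs (between-child SD 0.8 on the logit scale) gave at least one false difference in 92 to 95% of null runs with model-based standard errors. Child-level robust standard errors gave 5 to 6%, and equal-weight child means 4.5 to 6.1%.

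This fault does not depend on whether n means game trials or post-test items, but its size does depend on n. At SD 0.15 the same formula gives about 15% per pair for n = 30, and about 79% for n = 1,080 (12 sessions × 90).

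**Step 2: weighting, if n is game trials.** Without covariates, a group's fitted probability is total correct / total trials. Its distance from the mean of the children is

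shift = r × CV(n) × SD(accuracy).

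- n spread evenly over 80 to 100: CV = (20 / √12) / 90 = 0.064. The shift is 0.3 × 0.064 × 0.15 = 0.003 to 0.5 × 0.064 × 0.20 = 0.006, that is 0.3 to 0.6 points. With the relation present on one side only, the rejection rate with robust standard errors was about 5% at a nominal 5%.
- CV 0.3 to 0.6: the formula gives 0.3 × 0.3 × 0.15 = 1.35 points to 0.5 × 0.6 × 0.20 = 6.0 points. Simulation with skewed n gave 1.4 to 5.1 points.

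These are shifts within one group. They become differences between groups only so far as the other group does not share them. With the same r and the same CV in every arm they cancel. With r = 0.4 and SD 0.20 everywhere but CV 0.2 against 0.5, the difference is 0.4 × 0.3 × 0.20 = 2.4 points.

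**Step 3: direct check.** Two arms, each with half the children at 50% accuracy and half at 80%, so both have a child mean of 65.0%. Arm A has n = 90 throughout.

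| n in arm B (low / high accuracy) | Fitted, arm A | Fitted, arm B |
|---|---|---|
| 90 / 90 | 65.0% | 65.0% |
| 80 / 100 | 65.0% | 66.7% |
| 60 / 120 | 65.0% | 70.0% |

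The 80 / 100 row ties n perfectly to accuracy, which is why its 1.7 points exceeds the 0.6 above. When one arm has n = 45 for all and the other n = 90 for all, both stay at 65.0%. Equal child weights give a difference of zero in every case.

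**The case against.** **What n means is not settled.** The outcome is measured after the intervention and compared across five groups, yet the control group plays no game (Table 4). Post-test items would fit that, and the child does not choose how many of those there are. On that reading the weighting concern loses its basis. A child-varying n, and the article's use of the word trials for game trials elsewhere, fit the other reading. The ambiguity stands. It does not touch the independence fault.

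**The bias needs a difference between arms.** A reader might infer that the intrinsic groups will look better because they are predicted to play more. The documents do not support that: more trials in one arm alone gives no shift. The article does allow, for its companion regressions, that the effect of trials completed may be much greater under some feedback types. That makes an arm-specific relation plausible but not established, and the link between playing on and outcome is put only as something that could be argued.

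**Large error rates from weighting are not those of the planned test.** Rates of 7.5 to 27% arise for an uncorrected, unadjusted comparison of 60 with 60 children with wide variation in n. At 30 against 30 and the 0.005 level, the same inputs give about 0.7 to 2.6% per pair. Covariate adjustment could weaken the link further. This objection stands.

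**The analysis is supplementary, and detail may sit elsewhere.** The model is introduced as an addition, percentage accuracy is also regressed separately, and a fuller plan may specify robust errors. That limits the consequence. However, the article itself fixes the distribution, the varying n, the covariates and the comparisons, and that combination is unsound as written.

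**Conclusion.** The point holds in two parts of unequal weight. The larger is independence: as written, the model's standard errors are far too small under either reading of n. The false-positive rate is about 36 to 49% per pair at the 0.005 level, given about 90 trials per child and a between-child SD of 0.15 to 0.18. Those inputs are assumed, apart from the expected trial range.

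The smaller part is weighting. It applies only if n is game trials and only if the relation of n to accuracy, or the spread of n, differs between feedback types. It is then worth at most about 0.6 points at the expected 80 to 100 trials (with r up to 0.5), and about 1 to 5 points if the CV of n is 0.3 to 0.6. Robust standard errors cure the first part but not the second.

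The documents do not show that the comparison will be biased, or in which direction. Nor does this point reach the analyses of percentage consonants correct (PCC) or of phonological process occurrence.

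**What to change.** - Count each child once: model the child's proportion correct with a fractional-logit (quasi-binomial) model, or a generalised estimating equation weighted by 1/n, with child-level robust standard errors in either case. This deals with both parts.
- State that the target is the accuracy of the average child, which also aligns this model with the percentage-accuracy regression.
- State whether n is game trials or post-test items. If it is game trials, limit the comparison to the four feedback groups, since the control group has none; the Bonferroni divisor then becomes 4 × 3 / 2 = 6.

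The cost is a few lines of analysis wording, plus slightly wider intervals where some children complete few trials. No data collection changes.

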## Materials and equipment

### Participants

Children aged between 4 and 6 with phonological delay or phonological disorder as identified by a qualified speech pathologist using the Developmental Evaluation of Articulation and Phonology (DEAP; Dodd et al., 2002) will be randomly allocated to five groups, each with 30 participants. Phonological delay is defined as the consistent use of phonological processes that are used in typical development that are supressed by 90% of children of the same chronological age (Dodd, 2014). Phonological disorder was defined as the consistent use of phonological processes in which some of the phonological processes used by that child are not used by 90% of children at any stage of their development (Dodd, 2014). The children will all consistently use one or more of the three phonological processes to be targeted by the intervention of this study (stopping, fronting or cluster reduction). The severity of each child's diagnosis will be either mild, moderate or severe with reference to the normative data for percentage consonants correct (PCC) as measured by the DEAP.

All children will be monolingual English speakers with receptive language within or above the expected range for their age as measured by the Clinical Evaluation of Language Fundamentals –Preschool 2nd Edition (Wiig et al., 2006) or Clinical Evaluation of Language Fundamentals –Fourth Edition (Semel et al., 2006). Children will have hearing skills within normal limits as measured by their last hearing test within the last 12 months and will not have other symptoms of developmental delay as reported by parents. The children will also have no apparent deficits in structure and function in oromotor structure and function as determined by examination by a speech pathologist.

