A G-Power power analysis suggested a total sample size of 150 in order to detect a moderate to large effect size (*f* = 0.32) with 5% significance and 80% power. Our recruitment plan of 30 participants in each of our 5 conditions is consistent with the G-Power analysis suggestion to avoid type II error.

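### The additional binomial model makes no allowance for children differing in accuracy, so its standard errors will be too small and its Bonferroni comparisons anti-conservative

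*Protocol article*

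**What the plan says.** The Proposed analysis section of the protocol article lists three pieces of analysis.

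- A full-factorial regression on PCC, repeated for the other speech outcomes.
- A "Generalized Linear Model Analysis assuming a binomial distribution for the number of correct trials" after the intervention, out of n trials, where n may vary from child to child. The named adjustments are pre-intervention "language skills, age, and gender". The comparison rule is: "Marginal means will be compared for the five groups using a Bonferroni correction for multiple comparisons".
- A one-way ANOVA of motivation.

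For the second analysis, the article names no scale parameter, child-level random effect or robust standard error. It offers this model as a help in separating real-world simulation from verification feedback, and in judging articulation guidance. Those are the two factors of the 2 × 2 part of the design.

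The unit of randomisation is the child: children are "randomly allocated to five groups, each with 30 participants" (Participants). Allocation is stratified by severity (Recruitment of participants). Severity is a predictor in the PCC regression but is not named in the binomial model.

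The only trial counts in the article concern game play: "we expect that children will engage for up to 20 min completing 80–100 trials" (Session schedule), and "the exact number of trials completed by each child for each session will be recorded". The control group plays no game: "The control group will attend the first session and then return between 2 and 4 weeks later to take posttest".

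**The concern.** A binomial variance is right only if all children with the same covariate values share one probability of a correct response and their attempts are independent. The design makes that implausible. The children range from mild to severe and use one or more of three phonological processes. The stimuli are only 15 minimal pairs, and up to three attempts per word are allowed in the game. Language skills, age and gender will not absorb all of that spread.

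The counts will then vary more than the model allows. Intervals for the marginal means will be too narrow and p-values too small. Bonferroni divides the significance level by the number of comparisons; it does nothing about a wrong variance inside each one. At stake is a claim that one feedback type beats another when the data show only that some children in one group happened to be more accurate. The article intends the results to inform development of an application.

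**Working it through.** **The plan's own figure.** There is none for this model: the article gives no n, accuracy or correlation for it. The stated total of 150 is not tied to it. (A one-way five-group F test with f = 0.32, 5% and 80% needs 122, so 150 is not reproduced from that test; it lies on the safe side and does not bear on this point.)

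**Inputs from the article.** Five groups of 30, and Bonferroni across the groups.

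**Assumptions.**
- All pairs are compared: 5·4/2 = 10 comparisons, each at 0.05/10 = 0.005, so z = 2.807.
- n = 15, 30 or 90. The first two are one attempt per minimal pair or per word of the 15 pairs. The third is the middle of the game-play figure of 80–100, used only as an upper case.
- ρ, the within-child correlation left after covariates, is 0.02 to 0.10.
- Mean accuracy is p = 0.6. The between-child SD is √(ρ·p·(1−p)), which is √(0.05·0.24) = 0.11 at ρ = 0.05 and √(0.10·0.24) = 0.15 at ρ = 0.10. That is 11 and 15 percentage points.

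**Formulas.** Design effect DE = 1 + (n−1)·ρ. True SE / stated SE = √DE. Actual error per comparison = 2·(1 − Φ(2.807/√DE)).

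Example with n = 30, ρ = 0.05: DE = 1 + 29·0.05 = 2.45; √2.45 = 1.57; 2·(1 − Φ(2.807/1.57)) = 0.073 instead of 0.005.

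**Family-wise error** was simulated: null beta-binomial counts, five groups of 30, no covariates, ten pairwise tests. Where two values are shown, they come from two separate simulations.

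| n | ρ | DE | SE ratio | Error per comparison (nominal 0.005) | Family-wise error |
|---|---|---|---|---|---|
| 15 | 0.02 | 1.28 | 1.13 | 0.013 | 9% |
| 15 | 0.05 | 1.70 | 1.30 | 0.031 | 19–21% |
| 15 | 0.10 | 2.40 | 1.55 | 0.070 | 36–38% |
| 30 | 0.02 | 1.58 | 1.26 | 0.026 | 17% |
| 30 | 0.05 | 2.45 | 1.57 | 0.073 | 37–40% |
| 30 | 0.10 | 3.90 | 1.97 | 0.155 | 61% |
| 90 | 0.02 | 2.78 | 1.67 | 0.092 | 44% |
| 90 | 0.05 | 5.45 | 2.33 | 0.229 | 74–75% |
| 90 | 0.10 | 9.90 | 3.15 | 0.372 | 90% |

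With ρ = 0 the simulated family-wise error is about 4%, as expected of Bonferroni.

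**Check of the remedy.** Multiplying the variance by the estimated Pearson scale holds the family-wise error at about 3–5% in the same simulations. At n = 90 it is 3.3–4.0% for ρ from 0 to 0.30.

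**The case against.** Four objections have weight.

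1. **Size unknown.** The article gives neither n nor ρ. At n = 15 and ρ = 0.02 the standard error is off by only 13%. This stands, and it is why the result is given as a range.
2. **Condensed article.** A scale parameter or robust standard errors could be set in a full analysis plan that is not shown. That is possible. But the article does state the distribution, the covariates and the multiplicity rule, and followed as stated they give wrong error bars. If the full plan already has the correction, saying so closes the point.
3. **Additional analysis.** The PCC regression comes first, and PCC belongs to the primary measure. It and the motivation ANOVA use one value per child and estimate the residual spread from the data, so they do not share the fault. This stands and limits the consequence.
4. **Severity is stratified.** Balanced allocation keeps severity from driving differences between groups, so severity's share of the spread does little to raise the error rate. ρ should therefore be read as what remains among children of like severity. This tempers the size but does not remove the defect.

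A reader might also infer more than the documents support.

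- **80–100 trials as this model's n.** That is expected game play, recorded by session. The control group has no game trials, so a five-group comparison cannot rest on them. Nor does anything in the article pool the 12 sessions.
- **Standard errors several times too small.** At n = 90, a factor of 3 needs ρ of (9−1)/89 = 0.09. The documents give no such value.
- **Mostly false findings.** A high chance of at least one false result under a global null is not a majority of false results. With null share π, error per comparison a and assumed power 0.9, the false share is π·a/(π·a + (1−π)·0.9). At n = 90 and ρ from 0.01 to 0.30 (a from 0.04 to 0.59), this is 4–40% for π = 0.5 and 12–66% for π = 0.75.

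**Conclusion.** The concern holds for this one model. As stated, it lets children differ only through language skills, age and gender, so any further spread makes its standard errors too small and its Bonferroni comparisons anti-conservative. The direction is near certain; the size is conditional. For ρ of 0.05–0.10, the standard errors need to be larger by a factor of 1.30–1.55 (n = 15), 1.57–1.97 (n = 30) or 2.33–3.15 (n = 90). The chance of at least one false pairwise difference is then about 19–38%, 37–61% or 74–90%, against an intended 5%. These figures assume mean accuracy 0.6, ten comparisons, equal n per child and no true differences. Even the smallest n considered gives a material error at those correlations, so the undefined n does not rescue the model. The trial's main inference on PCC is not touched.

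**What to change.** Make the child the unit of the binomial analysis. Any of three models will do: a quasi-binomial GLM with the scale estimated from the Pearson statistic, a beta-binomial model, or a logistic model with a random intercept per child. The quasi-binomial is the smallest change: the marginal means stay as they are and only their standard errors move. Base every Bonferroni comparison of marginal means on the chosen model. Add severity as a covariate, since it is the stratification factor; otherwise its spread inflates the estimated scale. Define n, and take it from an occasion that all five groups share, since in-game trials exist for only four of them.

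The cost is one model option, a sentence defining the outcome, and wider intervals. No additional data or children are needed, and the change can be made before any data are seen.
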